### Outcomes

#### Primary Outcome

The eczema area and severity index (EASI) is one of the most widely used severity scales for assessing AD skin lesions, quantifying the severity of AD based on the area of involvement and the intensity of 4 clinical signs (erythema, edema or papulation, excoriation, and lichenification) in each body region [23]. The EASI score ranges from 0 to 72, with a higher score indicating a more severe disease condition. In this study, achieving an improvement of 75% or more in the EASI at week 16 from baseline (ie, EASI75) is designated as the primary outcome, calculated using the formula [(EASI at baseline – EASI at week *t*)/EASI at baseline] × 100%. The score will be evaluated at baseline, at every visit during the 16-week treatment period, and throughout the 36-week follow-up.

#### Secondary Outcomes

##### Overview

Secondary outcomes include the following assessments evaluated from baseline to week 52: EASI, body surface area (BSA), Investigator’s Global Assessment (IGA), Dermatology Life Quality Index (DLQI), numerical rating scale (NRS) for pruritus, Patient-Oriented Eczema Measure (POEM), Atopic Dermatitis Control Tool (ADCT), and TCM symptom scale. The EASI score, BSA, IGA, NRS, and ADCT scores will be evaluated at baseline and during the treatment and follow-up period. DLQI, POEM, and TCM syndrome scale scores will be assessed at baseline, during the treatment period, and at week 52.

##### Body Surface Area

The BSA is an assessment tool used to estimate the percentage of total BSA affected by skin lesions. Dermatologists estimate BSA using the “rule of nines,” in which body regions are assigned multiples of 9% (9% for the head and neck, 9% for each upper extremity, 18% each for the anterior and posterior trunk, 18% each for the lower extremities, and 1% for the perineum), or the “palm method,” whereby the patient’s own palm approximates 1% of the total BSA. In this study, the BSA score will be evaluated at baseline, every 2 weeks until week 16, and then every 4 weeks until week 52.

##### Investigator’s Global Assessment

The IGA is a single-item, clinician-reported instrument designed to rapidly grade a patient’s overall disease severity at the time of evaluation. It uses a 6-point ordinal scale (0=clear, 1=almost clear, 2=mild disease, 3=moderate disease, 4=severe disease, and 5=very severe disease). The score is based on a composite judgment of the degree of erythema, infiltration, and papulation [24]. This indicator will be assessed at baseline, every 2 weeks until week 16, and then every 4 weeks until week 52.

##### Dermatology Life Quality Index

The DLQI is a validated instrument designed to measure the impact of skin conditions on quality of life over the previous week [25]. It comprises 10 items assessing 6 domains: symptoms and feelings, daily activities, leisure, work and school, personal relationships, and treatment-related problems. Each item is scored on a 4-point ordinal scale (0=“not at all,” 1=“a little,” 2=“a lot,” and 3=“very much”). The total score ranges from 0 to 30 and is calculated by summing all item scores, with higher scores indicating greater impairment in quality of life. In this study, the DLQI will be evaluated at baseline, every 2 weeks until week 16, and at week 52.

##### NRS for Pruritus

The NRS is a single-item, patient-reported instrument designed to quantify itch severity over the previous 24 hours. Patients are asked to select a numerical rating from 0 to 10, where 0 represents “no itch” and 10 represents “the worst imaginable itch” [26]. This study will assess NRS for pruritus at baseline, every 2 weeks until week 16, and then every 4 weeks until week 52.

##### Patient-Oriented Eczema Measure

The POEM is a self-assessed measurement tool used to assess the frequency of 7 symptoms over the previous week: itching, sleep disturbance, bleeding, weeping or oozing, skin cracking, skin flaking, and skin dryness or roughness. Patients record the frequency of each symptom using a 5-point scale (0=no days, 1=1‐2 days, 2=3‐4 days, 3=5‐6 days, and 4=every day). The total POEM score is the sum of all 7 items, ranging from 0 to 28, with higher scores indicating more severe symptoms [27]. In this study, the POEM will be evaluated at baseline, every 2 weeks until week 16, and at week 52.

##### Atopic Dermatitis Control Tool

The ADCT is designed to assess patient-perceived AD control. It consists of 6 items that patients answer based on their experience over the previous week. These items cover multiple core domains of AD control, including the patient’s perception of AD symptoms, itch, brother, sleep, daily activities, and emotions. Each item is scored using a 5-point response scale ranging from 0 (no problem) to 4 (worst). The total ADCT score is calculated by summing the scores of all 6 items, ranging from 0 to 24, with higher scores indicating poorer disease control. In clinical practice, an ADCT score of 7 or higher is considered indicative of inadequately controlled disease [28]. In this study, the ADCT will be evaluated at baseline, every 2 weeks until week 16, and then every 4 weeks until week 52.

##### TCM Symptom Scale

The TCM symptom scale is a nonquantitative assessment instrument consisting of 2 primary components: local symptom evaluation and systemic symptom evaluation. The local assessment focuses on skin lesion characteristics and pruritus severity, whereas the systemic evaluation systematically documents facial complexion, sleep quality, dietary preferences, bowel and urinary habits, tongue coating, and pulse characteristics. The assessments of the TCM syndrome scale will be conducted at baseline, every 2 weeks until week 16, and at week 52.

### Sample Size

The improvement of 75% or more in the eczema area and severity index (EASI75) response rate at week 16 will be adopted as the primary efficacy outcome in this study. On the basis of prior data [29], a 57% response rate will be assumed in patients with biologic treatment (group G; *p*_1_= 0.57), and a 70% response rate will be assumed for the TCMIB group (groups A-F; *p*_2_=0.70). A 2-sided significance level (α) of .01 and a statistical power (1 − β) of 0.90 are specified. According to the sample size calculation formula n = (μ_α/2_ + μ_β_)^2^ × [*p*_1_(1 − *p*_1_) + *p*_2_(1 − *p*_2_)]/(*p*_2_ − *p*_1_)^2^, and considering a 15% dropout rate, at least 472 patients should be enrolled in each group. The final sample size is determined to be 500 patients per group. A total of at least 3500 participants are planned to be enrolled. Additionally, each participating hospital is expected to recruit a minimum of 100 patients, with at least 10 patients in each of the 7 treatment groups.

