**Methods:**

A total of 3500 patients with moderate to severe AD will be classified into 7 groups based on clinical manifestations and receive 16 weeks of treatment followed by 36 weeks of observation. A reduction of 75% or more in eczema area and severity index score from baseline to week 16 is set as the primary outcome. The secondary outcomes include the eczema area and severity index, body surface area, Investigator’s Global Assessment scale, Dermatology Life Quality Index, numerical rating scale for pruritus, Patient-Oriented Eczema Measure, Atopic Dermatitis Control Tool, and TCM syndrome scale. Assessments will be performed at baseline, every 2 weeks until week 16, and then every 4 weeks until week 52. Safety assessments include vital signs, concomitant medications, and adverse events. The SAS software (version 9.4) will be used for data analysis, and a *P* value of less than .05 will be considered statistically significant.

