### Statistical Analysis

This study will use the SAS software (version 9.4; SAS Institute) for statistical analysis. The reasons for missing data will be analyzed, and the multiple imputation method will be used for data completion. Statistical description and analysis will be performed on demographic characteristics and efficacy evaluation data. Quantitative variables following a normal distribution will be described using means and SDs and analyzed using either the 2-tailed *t* test or 2-tailed paired *t* test. Skew-distributed quantitative variables will be summarized as medians and IQRs and analyzed using the Wilcoxon rank-sum test. The quantitative variables of repeated measurement will be analyzed via repeated-measure ANOVA. Qualitative variables will be expressed as frequencies and percentages. The comparison between groups for categorical data will be conducted using the chi-square test, whereas repeated-measurement categorical data will be analyzed using the generalized estimating equations method. Generalized estimating equations models will be fitted with achievement of EASI75 response at each visit as the dependent variable and treatment regimen as the independent variable, adjusted for demographic characteristics (age and sex), medical history (family history and comorbidities), baseline disease severity (EASI, BSA, and IGA), and lifestyle factors (smoking and drinking). The working correlation structure will be selected based on the minimum quasi-likelihood under the independence model criterion. In addition, subgroup analyses will be performed stratified by age, sex, and disease severity. In this study, a *P* value below .05 will be considered statistically significant.

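### The primary outcome is sized at two-sided alpha .01 but will be judged at P<.05, and the primary contrast (pooled A-F or six patterns against G) is not fixed

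*Protocol article*

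**What the plan says.** Three places in the protocol article bear on this.

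- **Sample Size** takes week-16 EASI75 as the primary outcome and specifies "A 2-sided significance level (α) of .01" with power "of 0.90 are specified". For group G, "a 57% response rate will be assumed in patients with biologic treatment"; for groups A-F taken together, "a 70% response rate will be assumed for the TCMIB group". After 15% dropout, "at least 472 patients should be enrolled in each group", which is then raised to 500 in each of seven groups.
- **Statistical Analysis** closes with the rule that a P "value below .05 will be considered statistically significant". It does not separate the primary outcome from the rest. The EASI75 model has treatment regimen as its explanatory variable, without saying whether that has two levels or seven.
- **Abstract, Methods** repeats the rule: a P "value of less than .05 will be considered statistically significant".

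Treatment Plan gives groups A to F traditional Chinese medicine plus dupilumab (TCMIB) and group G dupilumab alone. No section explains why .01 was used for sizing.

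**The concern.** The article gives two decision thresholds for the same outcome. A week-16 EASI75 result with P = .03 would count as positive under Statistical Analysis and the Abstract, and as negative at the level for which the study was sized.

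How much this matters depends on the primary test, which the article leaves open. Sample Size describes the contrast as one TCMIB group against G, yet applies the calculated number to every individual group. That fits six separate comparisons of a pattern with G better than one pooled comparison. With one test, a .05 threshold is merely looser than the design level. With six tests, each at .05, the chance of at least one false positive is several times higher than at .01.

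**Working it through.** **Inputs.** From Sample Size: p1 = 0.57, p2 = 0.70, two-sided alpha .01, power 0.90, dropout 15%, 500 per group. From Treatment Plan: six TCMIB groups and one shared control, G.

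**1. Reproduce the plan's figure.** The article's formula is n = (z_α/2 + z_β)² × [p1(1 − p1) + p2(1 − p2)] / (p2 − p1)².

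- Variance term: 0.57 × 0.43 + 0.70 × 0.30 = 0.2451 + 0.2100 = 0.4551. Squared difference: 0.13² = 0.0169.
- Alpha .01: (2.576 + 1.282)² × 0.4551 / 0.0169 = 400.7, rounded up to 401; 401 / 0.85 = 471.8, rounded up to **472**. This matches the article.
- Alpha .05: (1.960 + 1.282)² × 0.4551 / 0.0169 = 283.0 (282.95 unrounded), so 283; 283 / 0.85 = 332.9, rounded up to **333**.
- One-sided .01 would give 351, or 413 after dropout.

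The printed 472 therefore rests on two-sided .01.

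**2. What a pooled test would need.** For A-F against G at 6:1, still at .01 and 90% power, the number needed in G is (2.576 + 1.282)² × (0.2451 + 0.2100/6) / 0.0169 ≈ 247, or about 291 after dropout. The 472 is a 1:1 calculation, so the per-group sizing fits pairwise comparisons. The single A-F rate fits a pooled one.

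**3. Error rate, single pooled test.** At the declared threshold it is 5%; at the sizing level it is 1%.

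**4. Error rate, six tests sharing G.** With equal group sizes, any two test statistics have correlation 0.5. Under the global null the two-sided family-wise error is

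1 − ∫ φ(u) [Φ((c − √0.5 u)/√0.5) − Φ((−c − √0.5 u)/√0.5)]⁶ du,

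with c = 1.960 for .05 and c = 2.576 for .01.

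| | each at .05 | each at .01 |
|---|---|---|
| Either direction | 20.7% | 4.9% |
| In favour of TCMIB only | 10.4% | 2.4% |
| Either direction, if tests were independent | 26.5% | 5.9% |

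The second row drops the lower-tail term from the integral. A binomial simulation (200,000 runs, common rate 0.57) gave 20.1% and 4.7% with 425 per group, and 21.1% and 4.7% with 500.

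**5. Power if .01 is kept.** Evaluable per group: 500 × 0.85 = 425. With pooled variance under the null, 2 × 0.635 × 0.365 = 0.46355, so the null SE is √(0.46355/425) = 0.03303; the alternative SE is √(0.4551/425) = 0.03272. Power = Φ[(0.13 − 2.576 × 0.03303)/0.03272] = Φ(1.37) ≈ 91.5%. The same calculation with 500 evaluable gives 95.6%. At .05 with 425 it is 97.7%. A pooled A-F versus G test at .01 with 425 in each group has 99.6%.

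**The case against.** The strongest reply is that six tests appear nowhere in the article. Sample Size names one contrast, Treatment Plan divides patients into TCMIB and biologic only, and the model refers only to treatment regimen. On that reading a P<.05 rule gives the conventional 5% error with no inflation. Sizing at a stricter level than the test does not invalidate the test; it only enrols more patients than .05 would require. This stands as far as it goes: the 21% figure is conditional on the six-test reading. It does not remove the conflict, because one pooled test would still be sized at 1% and judged at 5%.

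A reader might infer that .01 was chosen to protect six comparisons, since it holds their family-wise error near 5%, and that the .05 rule therefore gives up protection that was built into the design. The article does not support that. It gives no reason for .01, and an equal split of .05 over six would be .0083. The closeness may be coincidence.

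Two further limits are fair. The 21% counts false results in both directions, so the risk of a false claim for TCMIB is about half that. And treatment is not randomised: the Discussion itself names unmeasured confounding, which may threaten a false claim more than the nominal level does.

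An analysis plan that is not shown could well hold a multiplicity procedure, so its absence here is no fault. The point rests only on two thresholds that the article itself states and that disagree.

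**Conclusion.** The contradiction stands. The primary outcome is sized at two-sided .01, the printed sample size depends on that level, and the declared rule is P<.05 without exception. The article also does not fix whether the primary test is one pooled comparison or six.

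The consequence depends on that choice: 5% instead of 1% for one pooled test; about 21% instead of about 5% for six two-sided tests (about 10% instead of 2.4% in favour of TCMIB). The six-test figures assume the global null, equal group sizes, unadjusted comparisons and a shared control. Unequal pattern groups or covariate adjustment would shift them somewhat; independence would give 26.5% and 5.9%. They do not show that the study as written has a 21% false-positive rate, because the article does not commit to six tests.

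**What to change.** In Statistical Analysis and in the Abstract:

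1. Name the primary contrast for week-16 EASI75: pooled A-F against G, the six patterns each against G, or both.
2. Apply the two-sided .01 used for sizing to the primary test or tests. Keep .05 for secondary analyses, labelled exploratory.
3. If the pooled and the six pattern comparisons are both confirmatory, test pooled A-F against G first at .01 and proceed to the six, each at .01, only if it is significant. No pattern test is then reached unless the pooled test rejects, so under the global null the chance of any false claim is at most 1%.

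The cost is wording and a stricter threshold for the primary claim. Pairwise power at .01 is already about 92% with 425 evaluable per group, so no more patients are needed. Analysis is planned to begin in June 2028, so the change can be made and dated before any primary result is seen.

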### Safety Assessment

In this study, safety assessment will encompass monitoring of vital signs, recording of concomitant medications, physical examination, and recording of all adverse events (AEs) and serious AEs (SAEs). Vital signs, concomitant medications, AEs, and SAEs will be monitored at baseline, throughout the treatment period, and at week 52, whereas physical examinations will be performed at baseline, week 16, and week 52. A comprehensive study schedule is provided in Table S3 in Multimedia Appendix 1.

In this study, an AE is defined as any untoward medical occurrence in a patient following the initiation of treatment, which includes the presence or worsening of any syndrome, symptom, or disease. An SAE refers to any event occurring during the study that results in any of the following outcomes: hospitalization, prolongation of existing hospitalization, disability, inability to work, congenital anomaly, life-threatening condition, or death. Throughout the treatment period, the dermatologists will closely monitor the patients’ conditions. When AEs occur, the dermatologists will provide appropriate care based on the clinical presentation and will document relevant details, including the onset date, severity, relationship to study therapy, and resolution date of each event. All AEs will be monitored and followed up on until they are alleviated or properly resolved. Participants with AEs can withdraw from the study immediately and will receive appropriate medical management without cost. All AEs and SAEs will be reported in accordance with relevant regulatory requirements.

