### Objectives

In this study, we plan to collect clinically relevant data from patients in a real-world setting. The primary objective of this study is to evaluate the efficacy and safety of TCMIB treatment at 16 weeks in patients with moderate to severe AD, and the secondary objective is to analyze data on the involvement of TCM in the diagnosis, treatment, constitutional regulation, and prevention of relapse in AD so as to provide methodological insights to obtain high-quality evidence and inform future in-depth research on AD treatment. The findings are expected to provide further evidence for standardizing TCMIB regimens in the treatment of AD.

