## Methods

### Study Design

This is a multicenter, prospective, real-world study that will be conducted at 28 hospitals participating in the National Clinical Research Center for Skin and Immune Diseases Real-World Big Data Collection Platform from October 2024 to September 2028. The hospitals are listed in Table S1 in Multimedia Appendix 1. On the basis of the “disease-syndrome” classification framework, patients will be assigned to 7 groups according to their specific clinical presentations (n=500 per group): heat accumulation in the heart and spleen pattern (group A), heart fire with spleen deficiency pattern (group B), spleen deficiency with dampness pattern (group C), wind heat and dampness pattern (group D), spleen deficiency with blood dryness pattern (group E), spleen and kidney yang deficiency pattern (group F), and other patterns (group G). Patients in all groups will undergo a 16-week treatment phase and then a 36-week follow-up period. Baseline is defined as the time of enrollment (week 0) prior to the initiation of any treatment. Assessments will be conducted at baseline, every 2 weeks until week 16, and then every 4 weeks until week 52. The flowchart of this study is shown in Figure 1.

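### AE, SAE and concomitant-medication collection is not scheduled at the eight follow-up visits from week 20 to week 48, which weakens post-treatment safety data and the reading of follow-up response

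*Protocol article*

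**What the plan says.** **Visits.** The Study Design section sets the calendar: "Patients in all groups will undergo a 16-week treatment phase and then a 36-week follow-up period", and "Assessments will be conducted at baseline, every 2 weeks until week 16, and then every 4 weeks until week 52".

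**Efficacy in follow-up.** The overview of secondary outcomes says "The EASI score, BSA, IGA, NRS, and ADCT scores will be evaluated at baseline and during the treatment and follow-up period". The individual sections on BSA, IGA, NRS and ADCT repeat the 4-weekly schedule.

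**Safety and medication.** The Safety Assessment section says "Vital signs, concomitant medications, AEs, and SAEs will be monitored at baseline, throughout the treatment period, and at week 52". The same section undertakes to record every AE and SAE, with onset and resolution dates for AEs, and to follow AEs until they settle. It gives the AE definition a start (first treatment) but no end, and it defines the serious category broadly: "An SAE refers to any event occurring during the study". The CRF, described under Data Collection and Management, has a section for medications and AEs, and no visit restriction is stated there.

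**Objectives.** The primary objective is to "evaluate the efficacy and safety of TCMIB treatment at 16 weeks in patients with moderate to severe AD". The secondary objective is to "analyze data on the involvement of TCM in the diagnosis, treatment, constitutional regulation, and prevention of relapse in AD".

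**Analysis.** The Statistical Analysis section fits a GEE model to EASI75 response at each visit, with treatment regimen as the independent variable and baseline characteristics as covariates. Therapy taken after week 16 is not among the covariates.

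**The concern.** The article distinguishes two follow-up patterns. Some measures are taken every 4 weeks to week 52. Others (DLQI, POEM, the TCM scale) are taken after treatment only at week 52. Safety events and concomitant medication are placed in the second pattern, although patients attend anyway. This is a stated rule and not merely a detail left out of a condensed article.

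Two things are at stake. The first is completeness and timeliness of post-treatment safety data. An event shortly after week 16 may first be asked about at week 52, and never by schedule in a patient who leaves in between. The article's own limitations paragraph expects some patients not to complete the 52 weeks.

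The second is interpretation of follow-up response. Regimens are not randomised and the study is observational, so what patients take after week 16 may vary, and may vary by group. Without reliably dated medication records, a good EASI at week 32 could be sustained response or the result of further treatment.

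**Working it through.** The plan gives no figure of its own on this point, and the sample size plays no part in it. The check is a count of visits and a comparison of sections.

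**Inputs**
- Treatment phase 16 weeks, follow-up 36 weeks, total 52 (Study Design).
- Visits every 2 weeks to week 16, then every 4 weeks to week 52 (Study Design).
- Safety and medication time points (Safety Assessment).
- Efficacy time points (Secondary Outcomes and its subsections).

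**Step 1: count the visits**
- Up to week 16: weeks 0, 2, ..., 16, so 16/2 + 1 = 9 visits.
- Follow-up: weeks 20, 24, 28, 32, 36, 40, 44, 48, 52, so (52 − 20)/4 + 1 = 9 visits.
- Follow-up visits named for AEs, SAEs and medication: week 52 only, so 1 of 9. Not named: 9 − 1 = 8.

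**Step 2: set the schedules side by side**

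| Item | Weeks 0–16 | Weeks 20–48 | Week 52 |
|---|---|---|---|
| EASI, BSA, IGA, NRS, ADCT | yes | yes, 4-weekly | yes |
| DLQI, POEM, TCM scale | yes | no | yes |
| AEs, SAEs, concomitant medication | yes | none named | yes |

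**Step 3: length of the gap**
- From the end of treatment-period monitoring to the next scheduled enquiry: 52 − 16 = 36 weeks, which is 36/52 = 69% of the study calendar.
- With collection at every follow-up visit, the longest interval falls from 36 weeks to 4, and coverage rises from 1 of 9 to 9 of 9.

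**Step 4: consequence for follow-up EASI75**
At a given follow-up visit, let *r* be the share of a group that is in response only because of therapy taken after week 16. The observed response rate is then the rate without that therapy plus *r*. The contrast between the TCMIB groups and group G is shifted by *r*(TCMIB) − *r*(G). The shift is zero if the two shares are equal. The documents give no rates of later therapy, so its size cannot be calculated. Dated medication records are what would allow it to be examined.

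**Step 5: what is outside the gap**
The primary outcome is EASI75 at week 16, and the primary safety horizon is also 16 weeks. Both fall before the gap begins.

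**The case against.** The strongest reply is that the article does not say events go unrecorded. It commits to recording all of them, AEs carry dates, the CRF section has no stated visit limit, and sites retain paper and electronic medical records. A week-52 collection can look back over the interval and need not rest on patient memory alone. The visit-level schedule in Table S3 is not shown and may be fuller. All of this stands. A reader might infer that safety and medication go unrecorded for 69% of the study. The documents do not support that; they support only that no collection is named at eight of nine follow-up visits.

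A reader might also infer that relapse cannot be assessed. That too goes beyond the text. EASI and IGA are scored every 4 weeks to week 52, so loss of response remains visible. Response regardless of later therapy is also a legitimate quantity in a real-world study. What remains is the narrower problem that sustained response and re-treated response cannot be told apart reliably.

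A third reply is proportionality: treatment ends at week 16, and three other scales are also skipped until week 52, so a lighter follow-up may be deliberate. That explains the schedule but does not reconcile it with an SAE window running through the study, or with an objective that includes "constitutional regulation, and prevention of relapse in AD". If Table S3 does schedule 4-weekly collection, it contradicts the Safety Assessment text, and the two still need to be aligned.

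**Conclusion.** The point holds for follow-up data only. As written, AE, SAE and concomitant-medication collection is scheduled at one of nine follow-up visits, with up to 36 weeks between scheduled enquiries and none after week 16 for patients lost before week 52. This is at odds with the article's commitment to full AE and SAE recording over the study. It also leaves follow-up EASI75 and the relapse-prevention objective open to confounding by therapy that is not reliably dated.

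The 16-week primary efficacy and safety objective is not affected. The number of events missed or recorded late, and the size of any confounding, cannot be derived from the documents: the 15% dropout allowance is not split by time, and no rate of later therapy is given. The conclusion assumes that the Safety Assessment text describes the schedule actually in use; Table S3 could not be checked. It is a change that should be made, not one that threatens the main result.

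**What to change.** Reconcile the Safety Assessment section, and Table S3, with the visit calendar in Study Design. Complete the existing medications and AE section of the CRF at every 4-weekly visit from week 20 to week 52. Record start and stop dates for each medication, including any AD therapy taken after week 16, and onset and resolution dates for each event. State that these data will be used when follow-up response and relapse are interpreted. No new endpoint is needed to close the gap, and nothing about treatment changes.

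The cost is a few minutes per visit at visits that already take place, plus an update to the schedule table. The sample size is unchanged. Patients already in follow-up will have incomplete entries for visits that have passed. The article reports 900 of 3500 recruited at submission, so at that point 3500 − 900 = 2600 patients could still have had complete follow-up records, as could any of the 900 not yet past week 16. The change loses value the longer it is delayed.
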